### Statistical analyses

Data analysis will be performed with SPSS 23 (IBM; Armonck, USA). Means and standard deviations of the demographic and injury-related variables and the clinical characteristics collected at baseline will be calculated. As normality assumptions may not be met with this small sample size, data distributions and all model assumptions will be checked for all analyses. If model assumptions are not met, data will either be transformed or analyzed using a non-parametric test, as appropriate. For data not normally distributed, median and interquartile range will be reported. Independent *T* tests will be used to check for an imbalance between groups. Nominal variables will be checked with *χ*^2^ tests and ordinal variable with the Mann-Whitney Test. Statistical significance will be set at a *p* value of 0.05. To accommodate likely occasional missing days, the repeated measures obtained by diaries will be analyzed with mixed effect models. The treatment effects will be examined using a repeated-measures ANOVA. In the case of significant baseline imbalance, post hoc analysis of covariance (ANCOVA) will be used on the change scores of the outcome measures with baseline scores as covariates. Intention-to-treat analyses will be conducted and presented as primary results. Additionally, a per-protocol analysis will be performed. Also, we will compare the eCBT-I and TAU group with regard to the percentage of participants who have improved (reduction ≥ 6 points on the ISI) and recovered (ISI < 10). We will use mixed effect regression models to explore whether treatment efficacy, i.e., the time-by-treatment effect, is modified by time since brain injury and by diagnosis (stroke versus TBI).

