### Outcomes

#### Sleep outcome measures

The primary outcome measure is the change in insomnia severity measured with the Dutch version of the Insomnia Severity Index (ISI) at posttreatment. The ISI consists of 7 items and uses a 5-point scale to measure to which extent participants experience insomnia. The total score ranges from 0 (no insomnia) to 28 (severe insomnia). A cut-off of 10 is used to indicate clinical levels of insomnia in this study, similar to other studies [20–22]. The Minimally Clinical Improvement Difference (MCID), which indicates the minimal improvement to be clinically significant, is a reduction of six points [23]. The internal consistency is adequate (Cronbach’s alpha = 0.74–0.78). The ISI is selected as it is sensitive to treatment response [22, 24] and used in comparable research worldwide, including the Netherlands [20, 21]. Secondary sleep outcome measures include overall sleep disturbances assessed with the Pittsburgh Sleep Quality Index [25] and the following sleep features derived from the sleep diary app: total sleep time, sleep onset latency, number of nocturnal awakenings, sleep efficiency, and subjective sleep quality.

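### The primary ISI test may be replaced after assumption checks by an unfixed transformation or rank test, which can remove the treatment effect in ISI points

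*Protocol article*

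**What the plan says.** Under Statistical analyses, the protocol article gives the treatment-effect analysis as "The treatment effects will be examined using a repeated-measures ANOVA". The same paragraph says that "data distributions and all model assumptions will be checked for all analyses", for the reason "As normality assumptions may not be met with this small sample size". If the checks fail, "data will either be transformed or analyzed using a non-parametric test, as appropriate". The article names no check, threshold, transformation or replacement test.

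Under Sleep outcome measures, the primary outcome is the change in ISI at posttreatment, on a scale from 0 to 28, and the minimal clinically important improvement "is a reduction of six points". The Sample size calculation powers the trial only for the time-by-group interaction of the ANOVA. Statistical analyses also plans comparisons of the percentages improved (a fall of at least 6 points) and recovered (ISI below 10).

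**The concern.** The rule applies to all analyses, so it reaches the primary one. It has two consequences.

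- **The effect measure can change.** The primary outcome and its benchmark are in ISI points. A difference on a log scale, or a rank-sum p value, is not a mean difference in points with a confidence interval.
- **The choice of test stays open until outcome data have been examined.** The wording allows a transformation or a rank test and does not fix which. The article's Recruitment section says that the outcome is self-reported by participants who know their allocation, so a primary test fixed beforehand matters more than usual.

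At stake is whether the trial ends with one pre-stated, interpretable primary estimate.

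**Working it through.** **Inputs from the protocol article:** 48 completers (24 per arm), f = 0.20, within-subject correlation 0.54, two measures, alpha 0.05, power 0.80.

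**Assumptions not in the article:** Shapiro-Wilk checks at 5%; ISI mean 17 and SD 4.5 at baseline; a 3-point fall in both arms; scores rounded and limited to 0–28; for the skewed case, a gamma shape with skewness 1.4.

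**1. The plan's own figure.** λ = N·m·f²/(1−ρ) = 48 × 2 × 0.04 / 0.46 = 8.35, with 1 and 46 degrees of freedom. Power is 0.807; N = 46 gives 0.790. The figure of 48 is reproduced. With two measures, this test is the t test on change scores. The effect is 0.834 SDs of change, or 0.834 × √(2 × 0.46) = 0.80 raw SDs. At the assumed SD that is 0.80 × 4.5 = 3.6 ISI points.

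**2. Do the candidate tests agree?** Four tests were applied to each of 6,000 simulated trials at the design effect: t test on change, Mann-Whitney on change, Mann-Whitney on T2 scores, and t test on log-scale change. They disagreed on significance at 0.05 in about 31% of trials. That share is over all trials, whether or not a check failed. If disagreement is as frequent when a check fails, the trials in which the switch fires and the choice matters are about 0.06 × 0.31 = 2% (one residual check) to 0.21 × 0.31 = 7% (four checks).

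**3. How often would a check fail by chance?** For normal data and independent checks, the chance is 1 − 0.95^k: 5% for one, 10% for two, 19% for four, 26% for six. With rounded ISI scores, simulation gives about 6% for one check on pooled change residuals, about 12–13% for two arm-wise checks, and about 21% for four arm-by-visit checks.

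**4. Power near normality.**

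| Analysis | Power |
|---|---|
| t test on change (the planned interaction) | 0.81–0.82 |
| Mann-Whitney on change | about 0.79 |
| Mann-Whitney on T2 scores | 0.75 |
| Check, then Mann-Whitney on change if it fails | under 1 point below the t test |

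**5. Power under skew** (unrounded scores): t test 0.79, Mann-Whitney on change 0.84, log transform 0.95.

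**6. Type I error of the two-stage rule.** It is 4.3–4.9% in one set of simulations. In another it is 5.5–5.7%, against 5.5% for the plain t test in the same runs. About 6.5–7% arises only if the most favourable result is picked once a check fails.

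**7. Is the switch needed for validity?** With 24 per arm, the t test rejects a true null in 4.6% of trials for exponential data and 3.9% for lognormal data. It is not needed to hold alpha at 5%.

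**8. The fixed alternative.** Adjusting T2 ISI for baseline gives a standardised effect of 0.80/√(1 − 0.54²) = 0.80/0.842 = 0.95. With 24 per arm and 45 degrees of freedom, power is 0.896.

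**The case against.** The strongest defence is that the switch does little harm as written. A reader might infer from it a rule that fires often by chance, loses power and inflates type I error. The documents support none of these.

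- **Chance firing** depends on a check that the article does not name. A rate near 30% needs six separate cell tests, including follow-up scores that are not part of the primary outcome.
- **Power** is almost unchanged near normality, and a switch gains power under real skew.
- **Type I error** rises only if someone picks the best result. The plan says as appropriate, which is not that.
- **The interaction** can be tested by ranks: with two measures it is the group difference in change, and Mann-Whitney on change addresses that contrast. The planned ANOVA has no baseline covariate to lose.
- **The ISI scale** is not abandoned altogether. The improved and recovered percentages, and medians with interquartile ranges, stay in ISI terms.

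All of this stands. It does not remove the core. The percentages are additional comparisons, and medians per group describe the data; neither is the primary treatment effect with its interval.

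The last defence is that the choice of check and replacement test belongs to a fuller protocol or SAP that is not shown. That holds for the missing detail, which is not the point here. The article does state a rule under which the primary analysis can leave the ISI scale, and naming the tests elsewhere would not undo that.

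**Conclusion.** The concern holds in a limited form. The plan makes the primary ISI test depend on checks of the outcome data and leaves the replacement open. After a switch, the primary result is not a mean difference in ISI points, and the candidate tests disagree on significance in about 31% of trials at the design effect.

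That figure rests on the assumed mean of 17, SD of 4.5 and near-normal rounded scores, and on the four candidates compared. It measures how far the choice of test can matter; it does not forecast how often the trial's conclusion would change. Much of the spread comes from including a test that ignores baseline, and the two tests on raw change agree far more often.

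The case for change is interpretability and a fixed primary test. It does not rest on lost power or on a raised false-positive rate.

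**What to change.** For the primary outcome, replace the switch with one fixed analysis on the raw ISI scale: T2 ISI on treatment with baseline ISI as covariate, or the equivalent mixed model. Report the mean difference in ISI points with a 95% confidence interval, whatever the checks show. Keep rank-based and transformed analyses as labelled sensitivity analyses.

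Take the interval from ordinary standard errors or small-sample-corrected robust ones, such as HC3 with t quantiles. At 24 per arm, uncorrected robust errors (HC0 with normal quantiles) reject a true null in about 7% of trials and a percentile bootstrap in 6.8%, so neither should be used uncorrected. HC3 holds the rate at about 5%.

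The cost is plan wording; no extra patients or data are needed. Power rises from about 0.81 to about 0.90 at the plan's inputs, but that gain comes from the baseline adjustment and not from dropping the switch. The downside is some loss of efficiency, possibly more than slight, if ISI change is strongly skewed: in the skewed scenario above, the log transform reached 0.95 where the raw-scale change test had 0.79.

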### Sample size calculation

Calculation of power and group size in a repeated measures design requires an estimate of the expected intraclass correlation coefficient (ICC, within subject correlation). We therefore resorted to a recent randomized trial of Dekker and colleagues (2020) on the effect of eCBT-I on ISI in people with insomnia. We used this intraclass correlation coefficient as indication of follow-up of ISI assessments across 6 weeks in our study population with acquired brain injury. That study reported an ICC of 0.54 for ISI assessments repeated across 6 weeks in 175 people suffering from insomnia without brain injury [33]. Calculation of power and group size moreover requires an estimate of the expected treatment effect size. Whereas treatment effects of eCBT-I are often reported to be of moderate to large size, we preferred to be somewhat conservative and expect a somewhat smaller than moderate effect in the population of TBI and stroke and therefore used *f* = 0.20. Calculation of the required sample size using G*Power [34] for ANOVA, with two repeated measures and ICC of 0.54, indicated that 48 completers would provide (2 × 24), at a significance of alpha = 0.05, sufficient power (1-beta = 0.80) for a minimal detectable time-by-group interaction effect of *f* = 0.20 (small to moderate).

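### Baseline-adjusted ANCOVA should be the unconditional primary analysis of ISI, not a step triggered by a baseline significance test

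*Protocol article*

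**What the plan says.** All of the relevant text is in the protocol article.

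- **Statistical analyses.** Baseline comparability is tested: independent T "tests will be used to check for an imbalance between groups", with chi-square and Mann-Whitney tests for nominal and ordinal variables, at a p value of 0.05. The treatment effect is examined by repeated-measures ANOVA without a baseline covariate. Adjustment then follows only on a condition: "In the case of significant baseline imbalance, post hoc analysis of covariance (ANCOVA) will be used on the change scores of the outcome measures", with the baseline scores as covariates.
- **Sleep outcome measures.** The primary outcome is the change in ISI at posttreatment (T2). Table 3 shows ISI collected at T1 in all participants.
- **Sample size calculation.** The trial is sized "for ANOVA, with two repeated measures and ICC of 0.54", with an effect of f = 0.20 and 24 completers per arm, which is said to give "sufficient power (1-beta = 0.80) for a minimal detectable time-by-group interaction effect".

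No other section provides for baseline adjustment of the group comparison independently of the imbalance test. A separate statistical analysis plan may exist, but this rule is one that the protocol itself sets.

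**The concern.** Allocation is random, so any baseline difference is due to chance. A significance test of that difference says nothing useful about whether adjustment is worthwhile. The case for adjusting rests on the correlation between baseline and outcome, which is known to be substantial before any data are seen.

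With two time points, the time-by-group test in a repeated-measures ANOVA is the t test on change scores. It subtracts the whole baseline difference, whereas regression to the mean calls for subtracting only part of it. A chance imbalance too small to be significant therefore moves the estimate, and the trigger never reacts.

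The sentence is also incomplete as a rule. Calling the ANCOVA post hoc does not settle whether it replaces the ANOVA or stands beside it. Nor does the text say whether the triggering imbalance must be in the outcome's own baseline score or may be in another tested variable. If the two analyses disagree, the reader cannot tell which one answers the primary question.

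**Working it through.** **Inputs.** From Sample size calculation: alpha 0.05, power 0.80, f = 0.20, m = 2 measures, rho = 0.54, N = 48 (24 per arm). The correlation is borrowed: "That study reported an ICC of 0.54 for ISI assessments repeated across 6 weeks in 175 people suffering from insomnia without brain injury". No ISI SD is given, so the unit below is the T1 SD. Equal SDs at T1 and T2 are assumed at first and varied in step 4.

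**1. The plan's own figure.** For the within-between interaction, lambda = f²·N·m/(1 − rho) = 0.04 × 48 × 2/0.46 = 8.35 on 1 and 46 df. The noncentral F gives power 0.807 at N = 48 and 0.790 at N = 46, so 48 reproduces. The implied difference in change is √(8.348 × 0.92 × 4/48) = √0.64 = 0.80 SD.

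**2. Residual variance.**
- Change score: 2(1 − rho) = 2 × 0.46 = 0.92
- ANCOVA: 1 − rho² = 1 − 0.2916 = 0.7084
- Ratio: 0.7084/0.92 = 0.77, equal to (1 + rho)/2, a reduction of 23%
- Allowing for estimation of the slope, factor 1 + 1/(N − 4) = 1 + 1/44 = 1.023: 0.77 × 1.023 = 0.79, a reduction of about 21%

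**3. Power at 0.80 SD, N = 48.** By noncentral t, the change score gives 0.807 and ANCOVA (45 df, slope cost included) gives 0.890. Simulation of 100,000 trials gives 0.81 and 0.89.

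**4. Sensitivity.** With s = T2 SD/T1 SD, the variance ratio is s²(1 − rho²)/(s² + 1 − 2·rho·s). Power is for an effect of 0.80 T1 SD.

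| Assumption | Variance reduction | Power, change vs ANCOVA |
|---|---|---|
| rho 0.54, s = 1.0 | 23% | 0.81 vs 0.89 |
| rho 0.54, s = 1.2 | 1 − 1.020/1.144 = 11% | 0.72 vs 0.76 |
| rho 0.54, s = 1.4 | 1 − 1.388/1.448 = 4% | 0.62 vs 0.62-0.63 |
| rho 0.40, s = 1.0 | 1 − 0.70 = 30% | not computed |
| rho 0.70, s = 1.0 | 1 − 0.85 = 15% | not computed |

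**5. What the trigger can see.** A t test with 24 per arm reaches p = 0.05 at about 2.013 × √(2/24) = 0.58 SD. By chance it does so in about 5% of trials for each variable tested.

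**6. Undeclared imbalance.** Given a baseline difference d, the change-score estimate has expectation 0.80 − (1 − rho)·d. About 17% of trials have a non-significant d of 0.35-0.57 SD in one direction or the other. With a mean d of about 0.44, the shift is 0.46 × 0.44 = 0.20 SD. When d runs against the effect, the estimate averages about 0.60 and power is about 0.57. When it runs with the effect, they are about 1.00 and 0.96. ANCOVA stays at about 0.80 with power about 0.88 either way.

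**7. If ANCOVA replaces the ANOVA when triggered (baseline test on ISI only).** Simulated power is 0.81 and type I error 0.044, against 0.89 and 0.050 for ANCOVA in every trial. Among trials with no true effect and a significant baseline difference, the change score rejects in about 16% and ANCOVA in about 4%.

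**The case against.** The strongest defence is that the plan hangs together. The hypothesis, the primary outcome, the sample size and the ANOVA all concern change from baseline, and the ANOVA delivers the power claimed for it. Over all randomisations the change-score estimate is unbiased and its type I error is 0.050. This stands, and it means that the point concerns efficiency and clarity, not validity.

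It is also fair that the size of the gain is uncertain. The ICC comes from people without brain injury. Because insomnia disorder is an entry requirement (Eligibility criteria), the baseline spread may be narrower than the spread at T2, which would shrink the gain. The 23% is therefore an upper figure for rho = 0.54 over the SD ratios of 1.0 to 1.4 considered.

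Two stronger readings are tempting and not supported:

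- A reader might infer that the primary analysis is selected by the data. The text names repeated-measures ANOVA for the treatment effect and calls the ANCOVA post hoc, so a fixed primary analysis with a conditional supplement is at least as natural. Step 7 applies only if ANCOVA replaces the ANOVA.
- A reader might infer that imbalance in any characteristic, such as age or diagnosis, sets off an ANCOVA that does not adjust for that characteristic. The text does not say this. Since the covariates are baseline scores of the outcomes, imbalance in those scores may be all that is meant.

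Both are ambiguities to remove, not demonstrated errors.

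**Conclusion.** The point holds as a free improvement that should be made; it is not a flaw that invalidates the trial. The planned analysis is sound on average and achieves about 0.81 power with 48 completers. Type I error is not inflated: it is 0.050 for the ANOVA alone and about 0.044 if ANCOVA replaces it when triggered.

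Adjusting in every case would lower the chance of missing the planned effect from about 19% to about 11%, given rho = 0.54 and equal SDs. With a T2 SD 1.4 times the T1 SD, the power gain all but vanishes. These figures apply to the T1-T2 comparison that was powered; an overall test across T1, T2 and T3 would differ.

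The second benefit is protection in the individual trial. In about one trial in six, an imbalance that the test does not flag shifts the change-score estimate by about 0.20 SD, in either direction. The adverse half should not be cited alone, because in the other half the change score overstates the effect and gains power. ANCOVA removes both distortions. Whichever way the ambiguous sentence is read, a baseline significance test should not decide whether an adjusted result is produced.

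**What to change.** - Pre-specify one primary analysis: ANCOVA of T2 ISI (or of the T1-T2 change) on treatment with baseline ISI as covariate, or the equivalent mixed model with a common baseline mean. Use it whatever the baseline comparison shows.
- Apply the same form to the other scale outcomes.
- Delete the imbalance condition and the baseline significance tests, and describe baseline data by group only.
- If the repeated-measures ANOVA is kept, label it as supportive.

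The cost is about two sentences of protocol or analysis-plan wording, settled before the data are analysed, and one degree of freedom. Baseline ISI is already collected and ANCOVA is already among the planned methods. The sample size of 48 can stay, with the extra power held as a margin because rho and the SDs are uncertain.

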### Recruitment, randomization, blinding, and treatment allocation

Participants will be recruited from five outpatient rehabilitation centers spread over the Netherlands (Heliomare Rehabilitation at Wijk aan Zee, Reade at Amsterdam, Rehabilitation Friesland at Beetsterzwaag, Basalt Rehabilitation at Delft and The Hague, and Adelante at Hoensbroek). Patients that are eligible based on the inclusion and exclusion criteria will be asked to participate. After informed consent is given, participants will complete the baseline measurement. Participants will then be randomly assigned to the eCBT-I or the TAU group. All participants will continue with standard rehabilitation care for various complaints, which do not specifically address insomnia (see Table 2). As complaints differ between persons, interventions differ as well. This care can include psychotherapy aimed at mood or other psychopathology, therapy aimed at cognitive functioning, physiotherapy, fitness, occupational therapy, and social work. The therapy dosage depends on different needs and capacity of participants. The variation in rehabilitation care between participants is expected to be similar for both groups and will be registered at follow-up by their clinicians. The TAU group will only receive standard rehabilitation care and can receive the eCBT-I after the study period. Participants can leave the study at any time for any reason without consequences. In case of withdrawal, participants will be asked to still do the measurements to control for attrition bias and a new patient will be included in accordance with the procedure. The measurements and intervention are not likely to have adverse consequences. Randomization will be done by a research randomizer program (www.randomizer.org) using permuted blocks to balance participants equal to both groups within centers. Treatment assignment is blinded, as researcher assistants, clinicians, and participants are unaware of number of included participants per center and not informed of this randomization procedure. Treatment allocation is not blinded for therapist and participant, as the nature of cognitive behavioral therapy does not permit blinding, but will be concealed until participants are recruited and baseline measurements are finished. Outcome assessment is self-reported and therefore not blinded for participant, but potential assessment bias of clinician or data collector on outcomes is excluded. Data collector is blinded for treatment allocation as well. Research assistant responsible for data input is blinded. See Table 3 for an overview of all measurements.

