### Eligibility criteria

Participants are eligible for inclusion if diagnosed with stroke or TBI and insomnia disorder according to DSM-5 criteria. Furthermore, they should be aged 18 or older and capable of using the Internet. Exclusion criteria are untreated sleep apnea, current or expected treatment with a main focus on fatigue or sleep during the study, unstable medication regiments, use of medication with insomnia as side effect, alcohol or drug abuse, and a major untreated or unstable medical or psychiatric condition. Users of sleep medication will be encouraged to finish medication before enrolment or to keep intake stable during the study period. Depending on type and dosage of medication, the physician will determine the period needed to exclude the influence of finishing sleep-related medication on the outcome measures.

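### The ISI recovery rate has no baseline condition, so a participant already below 10 at T1 counts as recovered without changing

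*Protocol article*

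**What the plan says.** Statistical analyses in the protocol article says "we will compare the eCBT-I and TAU group with regard to the percentage of participants who have improved", and defines two ISI percentages for that comparison: "improved (reduction ≥ 6 points on the ISI) and recovered (ISI < 10". The first is a change from baseline and matches the minimal clinically important difference given under Sleep outcome measures, which "is a reduction of six points". The second is an absolute score.

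Sleep outcome measures also says: "A cut-off of 10 is used to indicate clinical levels of insomnia in this study". That cut-off is not an entry condition. Eligibility criteria reads: "Participants are eligible for inclusion if diagnosed with stroke or TBI and insomnia disorder according to DSM-5 criteria". The remaining criteria in that section mention no ISI score.

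On timing, the recruitment section says: "After informed consent is given, participants will complete the baseline measurement". Randomisation follows. Table 3 lists the ISI at T1, T2 and T3 and not at enrolment.

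**The concern.** To have recovered, a participant must first have been above the line. The article draws that line at an ISI of 10 but does not require anyone to be above it at T1. A participant can meet the diagnostic criterion, score 9 or less at T1, score the same at T2, and enter the numerator of the recovery rate. The Objectives section plans to explore whether efficacy varies with insomnia severity, so the authors themselves expect baseline severity to vary.

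At stake is how one supplementary percentage can be read. It could be above zero in an arm where nobody changed. The difference between arms would be somewhat smaller than the difference in actual recoveries. With few participants per arm, an uneven split of low scorers could also move the contrast by chance.

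**Working it through.** **1. The plan's own figure.** The article gives no figure for either percentage. The only related number is the sample size, which sets the arm size used below. For a within-between interaction with N = 48, m = 2 measures, f = 0.20 and correlation 0.54, λ = N·m·f²/(1 − ρ) = 48 × 2 × 0.04/0.46 = 8.35. With (1, 46) degrees of freedom and alpha 0.05 the power is 0.807, and 48 is the smallest even N that reaches 0.80. The sample size reproduces and this point does not touch it.

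**2. The two rules applied to an unchanged participant with T1 ISI of 9.**
- Improved: the reduction is 0, which is less than 6, so not counted.
- Recovered: 9 is below 10, so counted.

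Only the second rule misclassifies. No entry criterion and no enrolment measurement keeps such a participant out.

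**3. Weight of one participant.** In an arm of 24, k unchanged low scorers add k/24: 4.2% for k = 1, 8.3% for k = 2, 16.7% for k = 4. If the rate is limited to those with T1 ISI of 10 or more, they add 0%.

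**4. How many there might be (illustration only).** The article gives no baseline ISI mean or SD. Assume a normal distribution and compute P(ISI ≤ 9) = Φ((9.5 − mean)/SD):

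| Assumed mean | SD 4 | SD 5 |
|---|---|---|
| 15 | 8.5% | 13.6% |
| 16 | 5.2% | 9.7% |
| 17 | 3.0% | 6.7% |

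Across 48 participants this is 48 × 0.030 = 1.4 up to 48 × 0.136 = 6.5. Widening the assumed mean to 14 to 18 gives about 2% to 18%.

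**5. Effect on the contrast (illustration only).** Let a share q of each arm start below 10 and stay there, and let p be the true recovery proportion among the rest. The reported rate is q + (1 − q)p, so the reported difference is (1 − q) times the true one. Assume p = 50% against 20%, and q = 10%:
- eCBT-I: 0.10 + 0.90 × 0.50 = 55%
- TAU: 0.10 + 0.90 × 0.20 = 28%
- Difference: 27 points instead of 30.

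Using the normal approximation for two proportions with 24 per arm, power is 0.59 for 50% against 20% and 0.47 for 55% against 28%.

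**The case against.** **The term already implies a case at baseline, and the article is condensed.** Recovery ordinarily presupposes illness, and a full protocol or analysis plan may fix the denominator. That would answer a complaint about missing detail. Here, however, the article states the rule, and the rule as stated misclassifies.

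**The sentence might be one joint criterion.** If a participant had to be both improved and recovered, an unchanged participant would not count. Each term has its own definition in brackets, which makes two separate rates the likelier reading. If a joint rate was meant, the sentence still needs to say so.

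**Low scorers should be rare.** Everyone must have a diagnosed insomnia disorder, which should thin the lower tail relative to an unrestricted normal curve. This stands: the percentages in the working are probably too high.

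**The comparison is still a fair one.** The proportion below 10 after treatment, compared between randomised arms, is a valid contrast with no systematic bias, because low scorers are balanced on average. This also stands. A reader might infer that the rule does not measure recovery at all, or that it favours one arm. The documents support neither: for the large majority expected to enter at 10 or more the rule does what its name says, and a tilt could come only from chance imbalance.

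**Restricting the denominator departs from intention to treat.** It does omit some randomised participants. But T1 is completed before randomisation, so the restriction defines a baseline subgroup in which the randomised comparison holds. Reporting the unrestricted proportion as well keeps everyone in view.

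**Conclusion.** The point holds for the recovery rate alone. As defined, it counts as recovered a participant who starts below the article's own clinical cut-off and stays there. The consequence is a rate inflated in both arms and a mildly diluted difference, at about 4 percentage points per such participant in an arm of 24. How many there will be cannot be known from the article. The 3% to 14% rests on an assumed normal baseline with mean 15 to 17 and SD 4 to 5, and is likely an upper view given the diagnostic requirement. The fall from 30 to 27 points further assumes the recovery proportions, a 10% low-baseline share in each arm, and that those participants stay below 10.

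A reader might infer that the improved rate has the same defect. It does not: a reduction of at least 6 points is measured from baseline. Its only limit is a floor, since a participant starting at 5 or less cannot fall by 6, which is a different matter and calls for no change. Nor does the point reach the primary outcome, the repeated-measures analysis or the sample size. These percentages are supplementary, and in the worked example power was only 0.59 even without the problem. This is a modest but cheap improvement.

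**What to change.** Replace the recovery definition with: ISI of 10 or more at T1 and below 10 at T2 (and, reported separately, at T3), among randomised participants whose T1 ISI was 10 or more. Alongside it, report the proportion with ISI below 10 in all randomised participants, labelled as post-treatment status and not as recovery. State the number in each arm with T1 ISI below 10. Leave the improved rate as it is, and make clear that improved and recovered are two separate rates.

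This takes a sentence or two and no new data, because the T1 score is already collected before randomisation. The small downside is that the recovery denominator loses the few low-baseline participants.
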